## Abstract

**Background:**

People with Severe Mental Illness (SMI) frequently experience problems with regard to societal participation (i.e. work, education and daily activities outside the home), and require professional support in this area. The Boston University approach to Psychiatric Rehabilitation (BPR) is a comprehensive methodology that can offer this type of support. To date, several Randomised Controlled Trials (RCT’s) investigating the effectiveness of BPR have yielded positive outcomes with regard to societal participation. However, information about the cost-effectiveness and budgetary impact of the methodology, which may be important for broader dissemination of the approach, is lacking. BPR may be more cost effective than Care As Usual (CAU) because an increase in participation and independence may reduce the costs to society. Therefore, the aim of this study is to investigate, from a societal perspective, the cost-effectiveness of BPR for people with SMI who wish to increase their societal participation. In addition, the budget impact of implementing BPR in the Dutch healthcare setting will be assessed by means of a budget impact analysis (BIA) after completion of the trial.

**Methods:**

In a multisite RCT, 225 adults (18–64 years of age) with SMI will be randomly allocated to the experimental (BPR) or the control condition (CAU). Additionally, a pilot study will be conducted with a group of 25 patients with severe and enduring eating disorders. All participants will be offered support aimed at personal rehabilitation goals, and will be monitored over a period of a year. Outcomes will be measured at baseline, and at 6 and 12 months after enrolment. Based on trial results, further analyses will be performed to assess cost-effectiveness and the budgetary impact of implementation scenarios.

**Discussion:**

The trial results will provide insight into the cost-effectiveness of BPR in supporting people with SMI who would like to increase their level of societal participation. These results can be used to make decisions about further implementation of the method. Also, assessing budgetary impact will facilitate policymaking. The large sample size, geographic coverage and heterogeneity of the study group will ensure reliable generalisation of the study results.

**Trial registration:**

Current Controlled Trials: ISRCTN88987322. Registered 13 May 2014.

## Background

High unemployment rates and general difficulty in undertaking activities are common among people with Severe Mental Illness (SMI) around the world [1–11]. The needs of these people comprise access to a broad array of services, which are not limited to clinical and humanitarian needs, but also include rehabilitation requirements such as support with societal participation, which is defined as engaging in meaningful daily activities [12, 13].

**Fig. 1 Fig1:**
[figure not shown]
Consort diagram. Abbreviations: C1 - Centre1, C2 - Centre2, C3 - Centre3, CED – Centre for Eating Disorders, BPR – Boston Psychiatric Rehabilitation, CAU – Care As Usual

Meaningful daily activities can be described as activities that fulfil a goal or purpose that is personally and/or culturally important, and are positively correlated with quality of life [14–16]. An example of such an activity is regular employment, which is associated with higher self-esteem, fewer psychiatric symptoms, general wellbeing and higher quality of life [17–19]. When it comes to engaging in meaningful daily activities, people with SMI experience environmental obstacles such as lack of opportunities and support or negative images of the clients’ potential on the part of possible employers and others in their environments. They also have to cope with personal obstacles such as self-stigmatisation, psychiatric symptoms and lack of social skills, employment skills and emotional stability. A combination of these barriers, which often reinforce each other, can lead to motivational problems and fear of failure [20]. As a result, more people with SMI are unemployed and undertake fewer activities outside the home than may be explained by the seriousness of their psychiatric symptoms. Support in the area of societal participation is therefore vital.

Over the years, various methods have been developed to offer support in engaging in work and other meaningful activities. However, only a few of these have been proven effective. An example of a well-documented, evidence-based approach to supporting the employment needs of patients with SMI is the Individual Placement and Support model of supported employment (IPS) [21–23].

Whereas IPS focuses mainly on regular paid employment, the Boston University approach to Psychiatric Rehabilitation (BPR) has a broader scope and also focuses on other forms of meaningful activities, housing, education, social contacts, and of course, work (regular and sheltered employment as well as voluntary work). The mission of BPR is to “help persons with psychiatric disabilities increase their ability to function successfully and be satisfied in the environment of their choice with the least amount of ongoing professional intervention” [24].

In recent years, a number of RCTs have been performed which investigate the effectiveness of BPR and results are partially positive. In the United States, Rogers et al. [25] investigated the effectiveness of Psychiatric Vocational rehabilitation (BPR in the vocational context) but found no differences in vocational or clinical outcomes compared to a control condition. However, the researchers made considerable enhancements to the control condition, which may have diminished the contrast between the experimental and control condition. Positive results were found by Shern et al. [26], also in the United States, who focused on street-dwelling individuals with psychiatric disabilities. They found that the experimental group experienced fewer psychiatric symptoms and a better quality of life than the control group. Also, the experimental group spent significantly less time on the streets and showed increased societal participation in terms of a greater likelihood to attend a day programme than the control group. In Italy, Gigantesco et al. [27] investigated a specific structured planning and evaluation approach called VADO (in English, Skills Assessment and Definition of Goals) which is inspired by BPR. They found greater improvement in the personal and social functioning in patients treated with VADO compared to routine care. Swildens et al. [9] performed a multisite RCT in the Netherlands with 156 SMI patients in outpatient MHC, sheltered living and inpatient rehabilitation units. This study covered all rehabilitation areas: work, education, structured activities, social contacts and living independently. Patients were randomised to BPR or Care As Usual (CAU) with follow-ups after 12 and 24 months. The rate of goal attainment was substantially higher in BPR at 12 and 24 months than with CAU. Also, BPR was more effective with regard to promoting social contacts and societal participation. However, both groups improved equally with regard to quality of life, and BPR was no more successful than CAU with regard to living independently.

Despite the positive results and the subsequent recommendation of BPR in the Dutch Guidelines for Schizophrenia [28], implementation in MHC practice is still limited. The lack of insight into the cost-effectiveness structure of BPR is one of the obstacles to implementation. For instance, BPR may be more intensive than CAU and require an initial time investment from caregivers, which could later be compensated by increased independency and the empowerment of the patient. Indeed, if BPR effectively improves the societal participation of patients with SMI according to their own wishes, and patients have fewer needs, this may promote long-term improvement in functioning and have a positive effect on costs for society. A cost-effectiveness study is required to provide answers to these and other cost-related matters, and the results –if positive- may lead to broader dissemination of the approach. Therefore, in this study we aim to analyse the cost-effectiveness of BPR compared to CAU from a societal perspective. To further support policymaking regarding implementation, the trial results will be used in different implementation scenarios to assess the budget impact of implementing BPR in the Dutch healthcare setting.

### Objectives/aims

The main objective of the research is to gain insight into the effectiveness and cost-effectiveness of the Boston University approach to Psychiatric Rehabilitation (BPR) compared to Care as Usual (CAU) for patients with SMI (aged 18–64 years) who wish to increase their societal participation.

The primary outcome criterion is change in societal participation, which is defined as the presence of meaningful activities: paid work, regular voluntary work, vocational training or academic study, or full-time care of a family [9]. Secondary outcome measures are: patients’ experience of success, quality of life, psychosocial functioning, recovery, self-efficacy, health status and realising patients’ personal rehabilitation goals. Furthermore, we will conduct a budget impact analysis (BIA) to estimate the consequences of the broader implementation of BPR in the Dutch healthcare system.

The main research question is:Is BPR effective as well as cost-effective with regard to societal participation compared to CAU after 12 months for patients with SMI between the ages of 18 and 64 who have a wish for change in this rehabilitation area?

Secondary research questions are:Is BPR an effective intervention with regard to societal participation, in terms of patients’ experience of success, quality of life, psychosocial functioning, recovery, self-efficacy, health status and realising patients’ personal rehabilitation goals after 6 and 12 months for our target group?What are the financial consequences of broader implementation of BPR in the Dutch healthcare system?

## Methods

### Study design

A multicentre two parallel arm Randomised Controlled Trial (RCT) with repeated measures will be used to compare the cost-effectiveness of BPR with CAU in improving societal participation.

CAU encompasses various approaches commonly used to support patients with SMI. These include generic programmes for mental health nursing care, social work and vocational rehabilitation. CAU is provided by multidisciplinary MHC teams with assertive outreach elements for patients who need more intensive contact (Flexible ACT teams) and by Dutch regional institutes for Residential Care (RIRC, Dutch acronym RIBW), which support independent living in the community and offer supported housing facilities [29–32].

Participants will be randomly allocated to either the experimental group or the control group. Outcomes will be assessed at baseline, 6 and 12 months. Based on main study results as well as dropout rate and degree of adherence, scenarios for implementation will be formulated and assessed for their budgetary impact. An overview of the study design is shown in Fig. 1.

### Participating centres/setting

The study will be conducted at two regional MHC centres and a Dutch regional centre for Residential Care. In addition, a specialist team for SMI patients with long and enduring eating disorders will participate in the study.

### Participants

The study will include a heterogeneous group of 225 adult outpatients with SMI who express a wish to increase their societal participation. SMI is characterised by psychiatric disorders with a long duration of treatment and severe dysfunction. In the Netherlands, approximately 160,000 patients between 18 and 65 suffer from SMI [33]. Although most patients in this group have a history of psychosis, the definition of severe dysfunction is not limited to those with psychotic disorders [34]. Some patients have multiple diagnoses such as varying combinations of psychotic disorders, bipolar disorder, anxiety disorders, personality disorders, eating disorders and drug addiction. All patients are care recipients of the participating organisation that supports independent living in the community and offers supported housing facilities, or of FACT teams [35] at the participating regional mental health care (MHC) centres. A pilot group of 25 patients with severe and enduring eating disorders –often in combination with other severe psychiatric diagnoses- will be included in the study to add insight into the effectiveness of BPR for this group of long-term mentally ill patients. Patients with eating disorders also face problems such as entering or re-entering the labour market and/or finding meaningful ways of spending the day. These patients are often hospitalised for extreme underweight, meaning that this group will consist of outpatients as well as inpatients.

MH professionals will assess eligibility for participation in the study according to the following inclusion and exclusion criteria:

#### Inclusion criteria

Patients are eligible for participation if they:Have been diagnosed with Severe Mental Illness (a diagnosis according to DSM IV, long duration of service contact and functional impairment which substantially interferes with or limits one or more major life activities [36]) and/or have a severe and enduring history of Anorexia Nervosa.Have expressed a wish for change in societal participation (work, education, daily activities outside the home).Are between 18 and 64 years of age.^1^Are willing to participate in the study.

#### Exclusion criteria

Patients will be excluded if they:Have received BPR in the four months preceding the start of the trial.Are admitted as inpatients to a MHC centre at the start of the study (except for patients with Anorexia Nervosa).^2^Are legally incompetent.

### Interventions

#### Experimental group: Boston Psychiatric Rehabilitation (BPR)

Patients in the experimental group will take part in rehabilitation sessions based on BPR, which uses a methodology that helps patients achieve and retain their rehabilitation goals [24, 37, 38]. The approach consists of four phases:Exploring: the client is supported in discovering what he/she wants to achieve.Choosing: the client is supported in choosing a goal in a rehabilitation area such as work or housing.Getting: the client is supported in carrying out the necessary interventions to attain the goal.Keeping: the client is supported in keeping the attained goal.

Patients do not need to have a clearly defined idea or plan for change in order to receive BPR because an important component of BPR is helping patients explore their options. Therefore, BPR attends to the needs of patients who have been suffering from mental illness for a long time and have lost confidence in their own ability to initiate change. Participants assigned to BPR will be offered at least one session every 2 weeks with an experienced BPR rehabilitation worker. There is no predefined maximum or minimum number of sessions that must be completed. Instead, patient and BPR worker plan sessions by agreement. However, BPR workers are obliged to offer one session every 2 weeks. The total number of sessions and duration of the period in which patient and worker cooperate will be registered. The intervention will be carried out by rehabilitation workers fully trained in the methodology (social workers, MH nurses, occupational and vocational therapists) who have practised with at least four patients under the supervision of a certified expert in BPR. Each participating centre will take part by involving at least four workers experienced in BPR in the BPR condition. Each worker will have an additional caseload of four research patients a year. In all three centres, a sufficient number of professionals with BPR training are available to carry out the intervention.

Fidelity in the experimental condition will be checked by means of a BPR fidelity measure, using criteria developed by the Dutch foundation for BPR ‘Stichting Rehabilitatie ‘92’ in collaboration with the Boston University Center for Psychiatric Rehabilitation. Independent registered BPR experts will use the instrument to blindly rate all patient treatment files involved in this study. Furthermore, BPR workers will receive regular feedback and supervision.

#### Control group: Care As Usual (CAU)

Patients in the control group will receive CAU conducted according to the guidelines for FACT teams [29, 35, 39, 40] and Dutch RIRCs [31]. These guidelines form a general outline of the philosophy of care for the target groups and the way care is delivered in daily practice. The FACT model, which was developed in The Netherlands [35], contains all elements of the internationally well-known Assertive Community Treatment (ACT) model [41], but FACT differs from ACT in that a FACT team also targets patients who function in a more or less stable manner. These multidisciplinary teams provide medical, psychiatric, social, financial and vocational support, which can be intensified according to the patients’ needs. Detailed information about the Dutch FACT model is described in the English version of the FACT Manual [42].

In the Netherlands, supported housing and supported independent living in the community for patients with SMI is provided by 21 RIRCs. RIRC’s are primarily concerned with patient’s daily activities but also offer some support with regard to participation in society [30, 32]. However, structural support with rehabilitation is often lacking.

In line with the experimental group, participants assigned to the control group will also be offered at least one session every 2 weeks targeting a wish for societal participation, with no predefined maximum or minimum number of sessions that must be completed. Patient and CAU worker plan sessions by agreement and the total number of sessions and duration of their cooperation will be registered.

Although MH professionals working according to FACT or RIRC guidelines (social workers, MH nurses, occupational therapists or employment specialists) may be familiar with rehabilitation, they have not received specific training in BPR. They offer additional support to patients in clarifying and achieving their rehabilitation goals on the basis of generic MHC models: mental health nursing care, social work and vocational rehabilitation programmes. All CAU workers have at least 1 year of experience with supporting SMI patients. Each participating centre will provide at least three experienced rehabilitation workers to the CAU condition and each worker will have an additional caseload of at most 4 to 5 research patients a year. In all three centres, a sufficient number of professionals without BPR training are available to carry out the intervention. Because of the generic nature of CAU, fidelity will not be measured in this condition. However, CAU workers will receive regular supervision according to the FACT and RIRC guidelines to ensure a high level of care.

#### Contamination between BPR and CAU

Because workers from BPR and CAU conditions work in the same team environment and come in contact with each other, some contamination between conditions is unavoidable. However, BPR is a complex method that cannot be properly applied without extensive training and ongoing methodological supervision. Moreover, our focus is on the possible added value of specific rehabilitation techniques and not solely on rehabilitation attitude, for example. We therefore believe that the contrast between conditions will be great enough to detect possible differences.

## Measures

All measures and related domains are summarised in Table 1. All instruments have been designed to be sensitive enough to measure change in patients with SMI. A mixture of self-reporting instruments and assessment by MH professionals is used, which is generally recommended for research with SMI patients [43].

**Table 1 Tab1:** Overview of outcome and other measures

Domain	Measurement
Primary outcome measures	
Societal participation in the past 6 months	Subscale Employment/Occupation of the Birchwood Social Functioning Scale
Current level of societal participation	Dutch National Societal Participation Ladder
Total hours of societal participation	Birchwood Social Functioning Scale and Health Consumption Questionnaire
Secondary outcome measures	
Patients’ psychosocial functioning from their own perspective	Birchwood Social Functioning Scale
Patients’ psychosocial functioning from the MHC team’s perspective	Activity and Participation Scale
Patients’ experience of goal attainment (yes/no)	Structured interview
Quality of Life	Manchester Quality of Life Schedule
Recovery	Recovery Assessment Scale
Self-efficacy	General Self Efficacy Scale
Cost-effectiveness outcome measures	
Generic health Status	12-item Short Form
Medical and Nonmedical costs	Health Consumption Questionnaire
Other outcome measures	
Sociodemographics	Structured interview
Psychiatric symptoms and remission	Brief Psychiatric Rating Scale
Overall level of psychological, social and occupational functioning	Global Assessment of Functioning, Symptoms and Disabilities version
Quality of the therapeutic relationship	Helping Alliance Scale
Intervention uptake	Drop-out and non-adherence

### Primary outcome measures

The first primary outcome measure will be *societal participation in the past 6 months*. This is expressed in paid work, voluntary work and schooling (yes/no). This measure will be derived from the subscale Employment/Occupation of the self-report Birchwood Social Functioning Scale (SFS) [44] using a hierarchical index to dichotomise whether or not there is an increase in societal participation at 6 and/or 12 months. The SFS was constructed to measure areas of functioning that are crucial for the community maintenance of people with schizophrenia (i.e. psychosocial functioning). The SFS focuses on fundamental characteristics of societal functioning and consists of seven subscales:

1) Social engagement/withdrawal, 2) Interpersonal behaviour, 3) Pro-social activities, 4) Recreation, 5) Independence-competence, 6) Independence-performance, 7) Employment/occupation.

The SFS proved a reliable and valid instrument for measuring psychosocial functioning with a high level of internal consistency (Full scale α = 0, 80, Factor loadings >0, 70).2.The second primary outcome is *current level of societal participation,* which will be measured using the Dutch National Societal Participation Ladder [45]. The Dutch National Societal Participation Ladder was developed for the Social Support Act (Dutch: WMO) and establishes the level of societal participation in six steps:

1 = severe social isolation, 2 = social contacts outside the home, 3 = participation in organised activities, 4 = having an unpaid job, 5 = having a paid job with support, 6 = having a paid job.

A flowchart is used to determine the right step. The bottom two steps are considered a low level of societal participation. The instrument was developed for use by local governments throughout the Netherlands and was implemented in 2008. In 2013, the instrument was used by 73 % of social services [46]. Findings from a pilot study in 2009 [45] and an evaluation study in 2011 [47], indicated that the definitions of the steps are good, the instrument leaves little scope for personal interpretation and is short, clear and easy to work with. The Dutch National Societal Participation Ladder will be further validated with the subscale Employment/Occupation of the self-report Birchwood Social Functioning Scale (SFS) [44].3.The final primary outcome measure is *total hours of societal participation.* This will be derived from the self-report Birchwood Social Functioning Scale (SFS) [44] and from a detailed questionnaire regarding Medical and Non-Medical costs based in part on the Tic-P by Hakkaart et al. [48] (see ‘Medical Costs’ for more information).

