
### Sample size

With regard to the main outcome measure, the power analysis was based on the earlier finding that the proportion of patients engaged in meaningful activities increased by 11.5 % for BPR compared to 0 % for CAU after 1 year [9]. With this expected difference in proportion of change in both conditions, the study will have a power of 80 % (alpha = 0.05, two sided) if complete data from 2 × 90 patients is obtained. Furthermore, with regard to the economic evaluation, SF-12D is used to calculate a preference-based utility index, SF-6D. In the preceding RCT, the SF-12D [58] was not used, but scores on the WHOQOL are available [74]. For patients with rehabilitation goals in the area of societal participation, the differences between BPR and CAU after one year were 1.23 (SD 2.18). Calculating the required power of the study with this parameter, only 60 patients in each condition are needed to achieve 80 % power. Power rises to 95 % with 90 participants in each condition, which is needed for the primary outcome measure. Taking into account an average dropout rate of 20 % and a maximum dropout rate of 25 % after one year follow up, at least 225 respondents with SMI are needed for this trial. The number of patients eligible but not willing to participate will be carefully monitored to support the BIA. A pilot will be conducted for the additional 25 patients with severe and persistent eating disorders who will also participate in this study, since no information is available on the differences in change that can be expected after a year with and without BPR support for this group.

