To analyse results on the main outcome, the difference in percentage of patients with increased participation in both groups after 1 year will be compared. Firstly, descriptive statistics will be performed with regard to the proportions of patients with increased participation. Secondly, risk differences yielding numbers needed to treat (NNT) will be calculated using (multilevel) regression models to be adjusted for research centre and employment in the year preceding the study. Other possible confounders such as sociodemographics, psychiatric symptoms and remission, quality of the therapeutic relationship or educational level of MH professional will be added if comparison between intervention group and control group shows differences between these groups despite randomisation. In addition, sensitivity analyses will be performed on all outcomes, including only respondents who participated in at least two contacts with the rehabilitation worker and excluding patients for whom the outcome was rated indirectly because they were not available for interviews at 6 and 12 months. Secondary outcomes are (I) continuous variables indexing quality of life, psychosocial functioning, recovery and self-efficacy and (II) binary variables indexing patients’ experience of success in achieving their rehabilitation goals (yes/no). Patients’ experience of success in achieving their rehabilitation goals could also be presented as an (III) ordinal variable (yes/no/partially). Means and proportions of these variables at baseline, 6 and 12 months will be modelled using both multilevel linear and logistic regression analyses in which each person (level 2) contributes three observations (level 1), making adjustments for participating centre, and other confounders. Treatment effects will be quantified using the Time (baseline, 6 and 12 months) × Group (BPR and CAU) interaction, assessing whether change in the outcome of interest over time differs significantly between the two groups. Effects of time stratified by treatment group will be calculated by linear combination of the appropriate terms in the model using the General Linear Model (GLM) procedure in SPSS.

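### The primary endpoint is defined inconsistently: three primary outcomes or one, a 6-and/or-12-month rule or 1 year, and two different activity lists

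*Protocol article*

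**What the plan says.** **Number of outcomes.** Objectives/aims names a single primary outcome criterion, change in societal participation. Sample size refers to one main outcome measure and states that "the study will have a power of 80 % (alpha = 0.05, two sided) if complete data from 2 × 90 patients is obtained". Statistical analyses (Primary clinical analyses) describes one main comparison: "the difference in percentage of patients with increased participation in both groups after 1 year will be compared". Table 1 and Primary outcome measures, however, list three primary outcomes: a binary measure from the Employment/Occupation subscale of the SFS, the level on the Societal Participation Ladder, and total hours. The third is introduced with "The final primary outcome measure is".

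**Time point.** Primary outcome measures derives the first outcome "using a hierarchical index to dichotomise whether or not there is an increase in societal participation at 6 and/or 12 months". The main research question asks about 12 months. The planning figure in Sample size is that "the proportion of patients engaged in meaningful activities increased by 11.5 % for BPR compared to 0 % for CAU after 1 year", and the main analysis compares the groups at that same time.

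**Activities counted.** The list in Objectives/aims ends with "vocational training or academic study, or full-time care of a family". Primary outcome measures says of the first outcome: "This is expressed in paid work, voluntary work and schooling (yes/no"; family care is not in that list.

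**The concern.** These are statements that cannot all stand, not details left for another document. A reader cannot tell which outcome, which visit or which list of activities defines a responder, and defensible readings could lead to different conclusions.

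The time rule is the clearest case. The first outcome looks back over 6 months. A patient whose activity began and ended in the first half-year could be a responder if an increase at either visit is enough, but not if only the 12-month assessment counts. The phrase is itself two rules: requiring an increase at both visits can only keep or lower the number of responders relative to 12 months alone, and accepting either visit can only keep or raise it.

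At stake are the meaning of the 5% level, the power, and the effect measure in the cost-effectiveness ratio. That ratio is expressed per gain in the proportion with increased participation, and the section does not repeat the time point or the activity list.

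**Working it through.** **1. The three conflicts side by side**

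| Item | Objectives/aims | Primary outcome measures and Table 1 | Sample size | Primary clinical analyses |
|---|---|---|---|---|
| Number of primary outcomes | one | three | one | one |
| Time point | 12 months | 6 and/or 12 months | 1 year | 1 year |
| Full-time family care | included | not listed | not stated | not stated |

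On number and time, three sections agree and the outcome section differs. On activities, two sections give lists and the lists differ.

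**2. What the stated alpha and power cover**

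Inputs from Sample size: two-sided alpha 0.05, power 80%, 11.5% against 0%, 90 complete cases per arm.

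Pooled two-proportion formula, with p̄ = (0.115 + 0)/2 = 0.0575:

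n = [1.96·√(2p̄(1−p̄)) + 0.84·√(p₁(1−p₁) + p₂(1−p₂))]² / (p₁−p₂)²
= (0.645 + 0.269)² / 0.115² = 0.835 / 0.013225 = 63.1, so 64 per arm (80 with continuity correction).

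Power at 90 per arm: Φ[(0.115·√90 − 0.645)/0.319] = Φ(1.40) = 91.9%.

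The stated 90 therefore does not reproduce; it is larger than its inputs require. That is a separate matter. What counts here is that the calculation covers one binary outcome at 1 year.

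**3. Error rate under two readings**

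- Only the 1-year binary comparison decides: one test, 5%.
- Any of three outcomes at 0.05 counts as success: 1 − (1 − 0.05)³ = 1 − 0.857375 = 14.3% if independent. The protocol gives no correlations. Simulating three equally correlated two-sided z-tests (2,000,000 draws) gives:

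| Assumed correlation | Family-wise error |
|---|---|
| 0.3 | 13.6% |
| 0.5 | 12.5% |
| 0.7 | 10.9% |
| 0.9 | 8.4% |

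**4. Power if either visit counts**

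The 0% control figure is a 1-year figure and need not carry over to an either-visit rule. Suppose the 11.5-point difference stays and the control rate is above zero (both assumptions). Power at 90 per arm is then 82.8%, 70.5% or 56.3% at control rates of 2%, 5% or 10%.

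**5. If alpha were split equally over three outcomes**

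At 0.05/3 = 0.0167 the critical value is 2.394. Power for 11.5% against 0% at 90 per arm is Φ[(1.091 − 0.788)/0.319] = Φ(0.95) = 82.9%. With an assumed 2% control rate and the same difference it is 69.2%.

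**The case against.** The strongest reply is that the document already singles out one test. Sample size ties alpha to one main outcome, and the analysis section gives one main comparison at 1 year; the research question agrees. The differing phrase on time sits in an instrument description and may mean only that the index is scored at each visit. The activity list there may be a summary of what the subscale covers. How several outcomes share alpha is often left to an analysis plan.

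Much of this stands. A reader might infer that the stated 5% error rate fails. The document does not support that: nowhere does it say that success on any one of the three measures is enough, and even a single either-visit responder rule is one 5% test. Conflicts over visit or activities raise the error only if the version is chosen after the data are seen. The independence figure is also an upper illustration, since all three measures target one construct and two draw on the SFS.

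Three other inferences should not be drawn:

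- That the ladder cannot register education. Only short step labels are printed, and the flowchart that assigns the step is not shown.
- That the ladder is unvalidated. The text says "The Dutch National Societal Participation Ladder will be further validated with the subscale Employment/Occupation", after citing a pilot and an evaluation study.
- That the 11.5% was obtained with the list that includes family care. A shared citation does not show this.

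The reply does not remove the contradictions. Three measures are still called primary where other sections have one, and the text defining the primary variable still gives a different time rule and list. An analysis plan may add detail, but the protocol's own sections must agree.

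**Conclusion.** The primary endpoint is stated inconsistently in number, time point and activities counted, and must be reconciled. The 5% error rate is intact if the 1-year binary comparison alone decides. It would be about 8% to 14% only if any of the three primaries at 0.05 counted as success, over assumed correlations from 0.9 down to independence. The effect of the time rule on power and of family care on the event rate cannot be sized from the document; the power figures above rest on assumed control rates and an unchanged difference. Because most sections already agree on one outcome at 12 months, the repair is small, but until it is made the deciding result is open to more than one reading.

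**What to change.** - State in Primary outcome measures and Table 1 that the single primary outcome is the SFS-based binary increase from baseline at the 12-month assessment, tested at two-sided 5%.
- Delete the words *6 and/or* from its definition and report the 6-month result as secondary.
- Make the ladder and total hours secondary, or test them in fixed order only after the primary is significant. The alternative is to keep them primary and state how alpha is shared. Under an equal split the binary outcome keeps 82.9% power on the planning figures, so power for that outcome does not force demotion; no power basis is given for the other two.
- Bring the lists in Objectives/aims and Primary outcome measures to one list that the SFS subscale can score. If it cannot capture family care, align the objectives to the outcome section.
- Name the same outcome, time point and list in Cost-effectiveness analysis.

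The cost is wording in the protocol, and in any analysis plan and registry entry, recorded before the outcome data are analysed. No extra patients or measurements are needed. The downside is that, unless alpha is shared, two outcomes lose stand-alone primary status.
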